### Interventions

#### ***Experimental group***

All patients in the experimental group were trained for one hour in a secure environment at the hospital in order to make sure the patients were able to use the technology. A room close to the acute emergency ward was set up to resemble the patient home with the installed technology. They received instructions and training from the health personnel in use of seven items, following a checklist to ensure they were able to use and handle the telemedicine technology (TT) equipment before departure (see list of items´section). The equipment consisted of a videoconference system with a webcam and a touch screen, which allowed the patient direct access to the hospital staff 24 hours a day. Furthermore they were supplied with a pulse oximeter, a spirometer, a thermometer, a nebulizer for aerosolized beta_2_ agonist inhalation, an oxygen compressor and a medicine box containing antibiotics (oral), prednisone (oral), sedative (oral) and beta_2_ agonists (inhalation) There was a USB connection from each monitoring device connecting them to the personal computer (PC) touch screen and data was transmitted via wireless broadband technology (Figure 1). All patients received all the equipment, even patients with reasonable oxygen saturations had to know how to operate the oxygen compressor in case they would need oxygen later on. Most patients were familiar with the spirometer, pulse oximeter, the oxygen supply and medicine from earlier visits to the hospital and from ambulatory visits so the most unfamiliar thing for the patients to use was the touch screen. However, since it only had one possible option (a ‘call hospital’ button on the touch screen) 1 hour of training was judged sufficient before departure.

**Figure 1 F1:**
[figure not shown]
**Photo of the telemedicine technology (TT) equipment used in the Virtual Hospital Trial (VHT).** The photo illustrates the TT equipment used in the patients’ homes and consisted of the following items shown in the photo from left to right: The medicine box containing antibiotics, inhalation medicine, corticosteroids and sedatives; the electronic nebulizer used for inhalation medicine; the touch screen with a built-in webcam; the oxygen compressor on the far right standing on the floor;. the spirometer, pulse oximeter, and thermometer in front of the touch screen were used to send physiological measurements every day to the hospital. Also, the patient phone, which is carried by the nurse working in the acute emergency ward, is in front of the touch screen.

##### 

**List of items** Checklist and training program for the TT group

1. Patient can use the “call hospital” button on the finger touch screen

2. Patient can perform an oxygen saturation and pulse measurement on the finger tip

3. Patient can perform a lung function measurement

4. Patient can use the oxygen supply

5. Patient can use the nebulizer and corresponding medicine

6. Patient can perform an “acute” call to the hospital

7. Know when to dial the Danish emergency number 112

Patients in the telemedicine technology group (TT group) were transported to their own home within a maximum of 3 to 4 hours after randomization. Upon arrival at home, all patients were asked to redo the seven-item checklist to ensure that the patients still were able to perform the necessary procedures of self-management using the home-monitoring devices, the medication and the technology. The patients were accompanied home by a nurse or a doctor together with a technician who installed the technology and the equipment, a procedure that normally would last half an hour. All patients kept the equipment until considered ready for discharge, and the equipment was physically removed immediately thereafter.

Scheduled contacts with the hospital staff were agreed upon before leaving so that the patient was prepared for daily ward rounds using the video screen at appointed hours. Additional ward rounds and checkups were only planned if judged necessary by the attending doctor. Unscheduled and acute contacts could always be effectuated by the patient pressing the ‘call hospital’ button on the touch screen, a close resemblance to the hospital bed where the patient has a red string to pull when in need of assistance from a nurse. When a patient activated the ‘call hospital’ button a phone carried by the nurse on call would immediately ring, and the nurse could then choose to either talk directly to the patient on the phone or to use a video conference system to contact the patient visually.

If the patient experienced technical problems with the equipment the patient was instructed to call a direct phone number instead or to dial the Danish emergency number 112.

#### ***Control group***

The medical treatment in both groups followed a strict standardized treatment program for COPD patients admitted due to an exacerbation (see list of standard treatment´s section).

##### 

**List of standard treatment** Standard medical treatment regime given in the two groups

• Corticosteroids (oral) Prednisolone 37.5 mg × 1 for 10 days

• Antibiotics (oral) amoxicillin and clavulan acid 500 mg × 3 for 7 days

• Beta-2 agonists and anticholinergics (inhalation) fenoterol and ipratropium bromide via nebulizer in specific intervals

• Oxygen therapy (nasal) when needed

• Sedative (oral) levomepromazine 5 mg × 1 only if needed

The patients allocated to the control group were informed that they would be hospitalized as usual, receiving the conventional standard hospital treatment for an exacerbation.

### Discharge criteria

Prior to the trial 20 Danish lung specialists were asked to write down criteria for discharging a patient with an exacerbation of COPD, and the five most popular criteria were then used in this trial as discharge criteria. The discharge criteria are not applied systematically in usual care in Danish hospitals, and some of the criteria may have delayed discharges that might otherwise have happened outside the trial situation.

Patients in both groups were considered ready for discharge by the attending doctor if they fulfilled the following five criteria: 1) slept >4 hours without awakening from respiratory symptoms, 2) FEV1 not decreasing, 3) clinically stable, 4) condition improved during admission, and 5) oxygen saturation >90 without oxygen or with the regular oxygen supply if they were long-term oxygen users.

### Implementation and organization of telemedicine technology at the acute emergency ward

For the first 9 months of inclusion it was the trial physicians and nurses from the telemedicine research unit at Frederiksberg Hospital who took care of the telemedical patients and operated the 24/7 ‘call center’. The research staff either stayed at the hospital during nights or contacted the patients from their own homes using a PC with the TT solution embedded. Later on, twenty experienced nurses working at the acute emergency department at Frederiksberg University Hospital were trained 4 hours each in operating the TT solution to take over the calls during evenings and nights. During the daytime the research unit remained on call. Nursing staff from the emergency department were instructed to treat the telemedical patients exactly the same way as they would treat them if they had been present at the hospital except from the physical contact, which of course was not possible.

Patients admitted to their own home were represented with a special color on the electronic patient boards in the acute emergency ward indicating they were not physically present in the acute emergency wards but that they were still admitted or ‘outmitted’, which became an everyday expression for a patient treated at home. At the organizational level, the bed in which the patient should have been placed in was kept empty to reflect a decrease in workload at the emergency ward having patients ‘outmitted.’ This was very meaningful in that the emergency staff did not feel as if further workload was being introduced as a result of new treatment modalities.

### Sample size

The trial was originally planned to be conducted as a trial of non-inferiority, which determined the method for calculating sample size based on a prior study where the estimated readmission rate was set to be 23.1% [13,14].

The sample size calculation assuming non-inferiority with a predefined margin of 20% or less, with 5% alpha-error and 80% power, showed that a patient number of 70 in each group was needed. The inclusion number was therefore originally set to be 175 patients with an expected drop out of 20%. However, the required sample size was not attainable in the planned study duration and inclusion was stopped as planned after 18 months. This meant that the study would not reach sufficient power, but reporting of the sample size determination will still be done according to the consort statement recommendation [15].

### Collection of data

All patient data were collected in a case record form (CRF) at baseline, during the intervention, at discharge and again at follow-ups 1, 3 and 6 months after discharge.

Data concerning physiological parameters (pulse, temperature, oxygen saturation, FEV1, and FVC) were collected by a project nurse or project physician or by the ordinary staff at the two hospitals during the ward rounds.

Data concerning readmissions, emergency room visits, rehabilitation, ambulatory visits, deaths, additional prescriptions of prednisone or antibiotics during hospitalization, and length of hospital stays were obtained by searching the hospital databases, The Danish National Patient Registry, and the Danish Civil Registration System, and also by asking the patients at the three follow-up visits. The only data that were solely self-reported from the patient and not obtainable in the hospital databases were the health-related quality of life questionnaires and if there had been any visits to the general practitioner due to COPD. The validated health-related quality of life questionnaires used were: the Saint George Respiratory Questionnaire, (SGRQ), the Clinical COPD questionnaire (CCQ), and the EQ-5D questionnaire, a standardized instrument developed by the Euroqol group.

Also, a user satisfaction questionnaire was handed out to patients in the TT group at discharge and to the nurses who engaged with the ‘outmitted’ patients using the telemedical equipment at the hospital.

The patient user satisfaction questionnaire consisted of 29 questions. Of these, 24 questions were presented in a 5-point Likert-scale (1 strongly disagree through 5 strongly agree) and 5 close-ended questions (yes/no). The questionnaire covers the patient experience in different settings such as the daily ward round, acute calls, the equipment use, and the patient’s general experience of the at home admission with telemedicine technology.

The cognitive status of each patient was evaluated in a substudy using a neuropsychological test battery, including verbal learning, memory capacity and attention and was also evaluated by a self-reported questionnaire: the Subjective Cognitive Functioning (SCF). In the substudy, the patient’s functional status was evaluated by the Instrumental Activity of daily living (IADL)questionnaire.

Another substudy evaluated the patients’ self-efficacy. Self-efficacy was measured using ‘The COPD self-efficacy scale’, which has been validated in a Danish version [16].

### Statistics

All analyses will be done using SAS software version 9.3 http://support.sas.com/software/93. Time to readmission after discharge due to an exacerbation will be assessed using a stratified Cox regression to relax the assumptions of proportional hazards. Differences in readmission rate over time will be assessed using multilevel mixed-effects linear regression analysis with unstructured variance matrix where the baseline values of the outcomes are used as covariates. *P* values below 0.05 will be considered significant for the primary outcome, and *P* values below 0.01 will be considered significant for secondary outcomes. Skewed variables will be power transformed if possible; otherwise, the variables will be transformed into dichotomous responses. Missing values will be replaced using multiple imputations [17]. Survival times will be plotted in a Kaplan-Meier survival curve. Differences between the two groups in prescription of additional antibiotics or steroids due to further exacerbation, need of non-invasive ventilation or mechanical ventilation, emergency room visits, visits to the general practitioner, lung function, bed days, and adverse events will be analyzed with an unpaired Student t-test if data are normally distributed or Mann-Whitney test if not. All categorical data will be analyzed with Chi-square test or Fishers exact test as appropriate. For the health-related quality of life scores, differences from baseline, both within and between study groups, and 95% confidence intervals will be calculated. All analyses will be done on the principle of intention to treat.

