### Purpose

The overall aim of this study was to investigate a telemedicine-based treatment solution for patients with acute exacerbation of COPD at home compared to conventional hospital treatment as measured by first treatment failure, which is defined as readmission due to COPD within 30 days after discharge. Use of additional medicine and healthcare services due to COPD, mortality rate, physiological parameters, and health-related quality of life, healthcare costs, adverse events and user satisfaction are also evaluated.

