## Methods

### Design

This was a consecutive, randomized, open, parallel group, multicentre trial design. The study was planned as a PhD study with a duration of 3 years, starting with 18 months of enrollment (June 2010 to December 2011). All enrolled patients were followed for 6 months at follow-up visits 1, 3 and 6 months after discharge. Follow-up finished in May 2012.

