### Outcomes

#### ***Primary outcome***

The primary outcome was treatment failure defined as:

Readmission due to an exacerbation in the chronic obstructive lung disease within 30 days.

Only readmissions occurring after being discharged from the telemonitoring group or the usual care group was designated a readmission. Patients in both groups were discharged when fulfilling five pre-specified discharge criteria and all telemonitoring equipment was removed from the patient’s home the same day of discharge.

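### The stated reason for stratifying the Cox model does not cover the treatment hazard ratio, and no single analysis is designated for 30-day readmission

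*Protocol article*

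**What the plan says.** All places are in the protocol article.

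- **Primary outcome section:** treatment failure is "Readmission due to an exacerbation in the chronic obstructive lung disease within 30 days". The Purpose section starts the window at discharge: "first treatment failure, which is defined as readmission due to COPD within 30 days after discharge".
- **Sample size section:** the trial was originally planned as a non-inferiority trial, with an assumed readmission rate of 23.1%, a margin of 20%, 5% alpha-error and 80% power. This gave 70 per group, or 175 in total with 20% drop-out.
- **Design section:** "All enrolled patients were followed for 6 months at follow-up visits 1, 3 and 6 months after discharge".
- **Statistics section, three routes to a readmission test:**
  - The time-to-event model: "Time to readmission after discharge due to an exacerbation will be assessed using a stratified Cox regression to relax the assumptions of proportional hazards"
  - A second, longitudinal model named for readmission: "Differences in readmission rate over time will be assessed using multilevel mixed-effects linear regression analysis with unstructured variance matrix"
  - A general rule that would take in a yes/no outcome: "All categorical data will be analyzed with Chi-square test or Fishers exact test as appropriate"
- **Statistics section, significance level:** 0.05 is set for the primary outcome and 0.01 for secondary outcomes. None of the three methods is named as the one to which 0.05 applies.

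**The concern.** The clause about relaxing proportional hazards carries no qualification, and the comparison the trial exists to make is between the treatment groups. A reader will take the clause to mean that the treatment result is protected against non-proportional hazards. Stratification does not give that protection.

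The outcome and the sample size concern a proportion at a fixed 30 days. The Cox sentence gives a hazard ratio with no stated horizon, in a trial that follows patients for 6 months. With two other readmission analyses listed and one 0.05 level not assigned to any of them, the analyst could choose the primary P value after seeing the results. At stake is which number carries the trial's main conclusion, and whether it answers the 30-day question.

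**Working it through.** **1. The plan's own figure.** Inputs from the Sample size section: 23.1% assumed in both groups, margin 0.20 read as an absolute difference, 80% power. The 5% alpha is read as one-sided 2.5%.

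n per group = (1.960 + 0.842)² × 2 × 0.231 × 0.769 / 0.20² = 7.85 × 0.3553 / 0.04 = 69.7, so 70. Then 140 / 0.80 = 175.

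Both stated figures reproduce. A one-sided 5% gives 55 per group and does not. The trial was therefore sized on a difference between two 30-day proportions. The sample size is not in dispute.

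**2. What stratification relaxes.** In stratum s, with treatment indicator x, the model is h(t) = h0s(t) × exp(βx).

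- *Stratum is something other than treatment, such as hospital.* Within each stratum, the treated-to-control hazard ratio is h0s(t)exp(β) / h0s(t) = exp(β) at every t. The free baseline cancels, so proportional hazards for treatment is assumed exactly as before.
- *Stratum is treatment.* x is constant within each stratum, so exp(βx) cancels from every risk set and the partial likelihood does not contain β. In a check on 2,000 simulated patients, the log-likelihood was −9506.66 at β = −1, 0 and 1. The curves may differ freely, but there is no treatment estimate or P value from β.

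**3. Whether the horizon matters.** This uses an illustrative scenario, with assumptions chosen to show the mechanism and not taken from the article.

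- Control hazard: −ln(1 − 0.231)/30 = 0.00876 per day throughout.
- Treated hazard to day 30: −ln(1 − 0.431)/30 = 0.0188 per day. The hazard ratio is 0.5639/0.2627 = 2.15, the hazard-ratio equivalent of a 20-point excess.
- Treated hazard after day 30: 0.25, 0.4 or 0.5 times the control hazard.

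Cox fits to 20,000 simulated patients per group gave these treatment hazard ratios:

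| Later ratio | Censored at day 30 | Censored at day 180 |
|---|---|---|
| 0.25 | 2.18 | 0.75 |
| 0.4 | 2.13 | 0.87 |
| 0.5 | 2.19 | 0.98 |

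The direction reverses. Hand arithmetic on cumulative risk agrees. By day 180 the control cumulative hazard is 6 × 0.2627 = 1.576, a risk of 1 − exp(−1.576) = 79%. The treated cumulative hazard is 0.5639 + 5 × 0.2627 × r, which is 0.892 for r = 0.25 (59%) and 1.221 for r = 0.5 (70%).

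Stratifying by a two-level factor left the 180-day ratios unchanged to three decimals (0.750, 0.870 and 0.975 with and without strata). That factor was assigned at random and had no effect on the hazard, so this only illustrates step 2. The algebra is the proof.

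**4. The three listed analyses side by side.**

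- Stratified Cox: a hazard ratio, horizon not stated.
- Linear mixed model: readmission rate over time, a different quantity from readmission by day 30.
- Chi-square or Fisher: a generic rule for categorical data, which would include yes/no readmission by day 30. It is the only one that directly matches the defined outcome, and it is not linked to it.

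**The case against.** The case against is substantial.

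- **The Cox model is never called primary.** A reader might infer that it is, because it comes first in the Statistics section. The text says only that time to readmission will be assessed this way. This stands: the point is that no analysis is designated, not that the wrong one is.
- **The clause does not mention treatment.** Relaxing proportionality for a nuisance factor is a legitimate use of the method. This partly stands. The clause is true for the stratifier, but it is written without that limit, and for the treatment contrast it is not true. Nothing suggests that treatment is the stratum, so that branch only completes the argument.
- **Strata and censoring time may be in the full protocol or analysis plan.** This stands for those details alone, and their absence is not the point. A reader might go further and say the Cox model cannot address the 30-day outcome. That is not supported: censored at day 30 it would address the window, on the hazard-ratio scale.
- **The mixed model and the chi-square rule have other purposes.** This is fair as a reading of intent. But if the chi-square rule is the primary test, the article needs only to say so.
- **Non-proportional hazards are not shown to be likely.** This stands. One might infer them from the removal of equipment, but removal is on the day of discharge and time to readmission starts at discharge, so exposure does not change during the risk period. The later ratios in the working are assumptions.
- **The small sample is a separate matter.** With 57 patients, about 57 × 0.231 = 13 events are expected by day 30, and any estimator will be imprecise. The risk difference would have a 95% half-width of about 1.96 × √(2 × 0.231 × 0.769 / 28.5) = 22 points. Wide intervals are therefore no evidence against the Cox model, and the article already concedes low power.

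**Conclusion.** Two things hold. First, the rationale is wrong as written: stratification does not relax proportional hazards for the treatment effect, whatever the stratum. This follows from the form of the model and needs no assumption about the data. Second, the article lists three analyses that could each claim 0.05 for one primary outcome, and its time-to-event model is not tied to the 30-day window on which the outcome and sample size rest.

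The size of the second problem depends on the data. If the treatment hazard ratio is constant over time, the 30-day and 6-month Cox analyses target the same ratio. Under the assumed crossing hazards they point in opposite directions. The documents give no basis for predicting which case applies.

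They also do not support saying that the primary result will be invalid, or that a current margin test is compromised: non-inferiority is described as the original plan, and no present margin test is stated. This is a correction worth making, below the level of a must-fix.

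**What to change.** In the Statistics section:

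1. Designate the between-group difference in the proportion readmitted for a COPD exacerbation within 30 days of discharge, with its 95% CI, as the single primary analysis to which 0.05 applies. It may be stratified by hospital. This is the scale on which the trial was sized.
2. Keep the Cox model as supportive, with treatment as covariate, hospital as stratum and censoring at day 30.
3. Delete the clause about relaxing proportional hazards.
4. Label the mixed model for readmission rate as secondary.

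The cost is a few sentences, with no new data or patients. One caution: the abstract says results were analyzed in 2013, while the Statistics section is in the future tense. The designation should carry a date and say whether it was made before the results were seen. If it was not, it should be reported as a later clarification.

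### Readmission gets two named models and a general categorical test under one 0.05 threshold, and none is identified as deciding the 30-day primary outcome

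*Protocol article*

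**What the plan says.** Under Primary outcome, the protocol article defines treatment failure as "Readmission due to an exacerbation in the chronic obstructive lung disease within 30 days". Purpose makes clear that the 30 days run from discharge. This is a yes/no outcome with a fixed window.

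Under Statistics, two models are tied to readmission by name:

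- "Time to readmission after discharge due to an exacerbation will be assessed using a stratified Cox regression to relax the assumptions of proportional hazards". No time horizon is given, and Design has every patient followed for 6 months.
- "Differences in readmission rate over time will be assessed using multilevel mixed-effects linear regression analysis with unstructured variance matrix". Visits are at 1, 3 and 6 months.

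A general sentence adds: "All categorical data will be analyzed with Chi-square test or Fishers exact test as appropriate". It does not mention readmission, but a yes/no readmission outcome is categorical.

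The thresholds are that P "values below 0.05 will be considered significant for the primary outcome", and that P "values below 0.01 will be considered significant for secondary outcomes". No sentence says which readmission analysis the 0.05 level belongs to. The Secondary outcomes list contains no readmission item.

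**The concern.** The stated endpoint and the stated analyses do not line up. The endpoint is a 30-day proportion. Neither model named for readmission compares 30-day proportions, and the test that does so enters only through a general sentence. A reader told that the primary outcome was significant could not tell whether the P value refers to readmission within 30 days, to time to readmission over an unstated period, or to a rate across three visits.

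If more than one of these P values may be taken as the primary result, the 5% level is spent more than once. Few events are expected: 57 × 0.231 ≈ 13 readmissions within 30 days at the planning rate, or 57 × 0.285 ≈ 16 at the Danish rate quoted in the Discussion. With so few events, analyses over different windows can fall on different sides of 0.05.

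**Working it through.** **Inputs from the article.** Planning readmission rate 23.1%, margin 20%, alpha 5%, power 80%, 70 per group, 20% dropout, 175 in total (Sample size); 57 randomized (Results); 28.5% readmitted within a month (Discussion); visits at 1, 3 and 6 months (Design).

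**The plan's own figure.** Taking the margin as absolute, n per group = 2p(1−p)(z_α + z_β)² / margin².

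- One-sided 2.5%: 2 × 0.231 × 0.769 × (1.960 + 0.842)² / 0.20² = 69.7, so 70. This matches.
- One-sided 5%: 2 × 0.231 × 0.769 × (1.645 + 0.842)² / 0.20² = 54.9, so 55. This does not match.
- Dropout: 140 / 0.80 = 175. This matches.

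The trial was therefore sized on a non-inferiority comparison of proportions, with the 5% acting as a two-sided level.

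**Reference points if any significant test counts.**

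- Identical tests: 5%.
- Two independent tests: 1 − 0.95² = 9.75%.
- Three independent tests: 1 − 0.95³ = 14.3%.
- Three equally correlated normal test statistics: 12.5% at correlation 0.5, 10.9% at 0.7, 8.4% at 0.9.

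The article gives no correlation, so the tests were simulated under no treatment difference, with 4,000 trials per scenario and N = 57.

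**Simulation assumptions.**

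- 30-day risk 23.1% or 28.5%, constant hazard for each patient, with or without between-patient heterogeneity (gamma frailty variance 1), and complete 180-day follow-up.
- Cox model represented by its score test (log-rank), stratified by site. The article does not name the strata.
- Mixed model represented by repeated-measures group tests (main effect, joint, or interaction) on rates at the three visits, without the baseline covariate.

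| Tests that could be claimed | False-positive rate |
|---|---|
| Chi-square alone | 4.5-5.0% |
| Fisher alone | 3.0% |
| 30-day Cox or chi-square/Fisher | 4.9-5.8% |
| 180-day Cox or chi-square/Fisher | 7.2-9.2% |
| The two named models only (Cox, mixed) | 7.8-10.0% |
| All three, Cox cut at 30 days | 7.8-9.4% |
| All three, Cox run to 180 days | 9.6-12.3% |

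The Monte Carlo standard error near 10% is √(0.10 × 0.90 / 4,000) ≈ 0.5 percentage points.

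The third row shows that a 30-day Cox model and a 30-day proportion test are nearly the same test. The excess over 5% comes from adding the mixed model, from letting Cox run past 30 days, or both. It does not need the general chi-square/Fisher sentence, because the two named models alone give 7.8-10.0%.

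**How often the analyses part company.** In a separate null simulation (6,000 trials per scenario), chi-square or 6-month Cox was significant in 8.1-9.0% of trials. In 40-45% of those, Cox was significant without the 30-day test. Of all null trials, that is about 0.40 × 8.1% = 3.2% to 0.45 × 9.0% = 4.1%.

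**The case against.** The strongest reply is that the article never says a significant result on any one analysis makes the trial positive. That is correct. A reader might infer that the plan runs at 8-12% instead of 5%, but the text does not support it: the figure needs a decision rule the article does not contain. What the article contains is an ambiguity, and the figure measures the exposure if the ambiguity were resolved in the loosest way.

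Second, the chi-square/Fisher test is not assigned to readmission by name. This also stands, but the point does not depend on it.

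Third, the Cox and rate-over-time models may run to 6 months, answer a different question, and be meant as supportive. This is possible. Against it, the article does not call them supportive, no readmission item stands among the secondary outcomes to which the 0.01 level applies, and the 0.05 sentence directly follows the two models.

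Fourth, a condensed article commonly leaves the labelling of analyses to an analysis plan, and an unseen plan may settle it. The point here is narrower than missing detail: the article itself states the models and the threshold, and they do not match the endpoint it states.

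Fifth, the simulation uses stand-ins for the stated models and a no-difference null, whereas the trial was planned for non-inferiority. Both limits apply. No error rate for a non-inferiority claim was computed, and Statistics names no non-inferiority test.

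**Conclusion.** The point holds as an unresolved choice in the stated analysis. There is one 30-day primary outcome, two named models with unstated or different windows, a general test that also applies, and one 0.05 threshold with no decisive analysis.

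Its size is conditional. If any significant result could be claimed as primary, the false-positive rate at N = 57 would be roughly 8-12%, against reference points of 5% (identical tests) and 14.3% (three independent tests). If Cox is cut at 30 days and only it and the proportion test count, the rate is about 5-6% and there is little to correct. It is also not shown that a borderline result is likely in this trial; no calculation supports that.

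**What to change.** State in Statistics that the primary conclusion rests on one contrast: the between-group difference in the proportion of randomized patients with a COPD readmission within 30 days of discharge, with its 95% confidence interval, tested once at the 0.05 level with sidedness stated. State that the interval is also read against the originally planned 20% non-inferiority margin. Label the Cox and rate-over-time analyses as supportive and unable to make the primary outcome significant. If all three are to remain able to decide, 0.05 / 3 = 0.0167 for each caps the error at 5%.

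The Abstract says results were analyzed in 2013, while Statistics is in the future tense. If the analysis is already done, apply the same labelling in the report.

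The cost is one or two sentences, and a significant supportive analysis can no longer be claimed as the primary result. The interval will be wide. With an assumed 29 and 28 patients and equal true rates of 23.1%, its half-width is about 1.96 × √(0.231 × 0.769 × (1/29 + 1/28)) ≈ 22 percentage points, so the reading against the margin may well be inconclusive. That follows from the shortfall in recruitment, which the article acknowledges, and not from this change.
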